## 2. Methods

### 2.1. Design and Participants

This quasi-experimental study will be carried out in Cáceres (Extremadura, Spain). Convenience sampling will be conducted in six different Primary Schools. Three schools will be randomly assigned to the control school and the other three schools to the experimental school. The sample size will be estimated using the following formula: *n* = (Z)^2^ (*p*(1 − *p*) e^2^), where “*n*” is the sample size, Z = 1.96 (95% confidence interval), *p* = number of 4th and 5th primary school students in the city where the study will be conducted (±3350 students), and e = margin of error (3%). The minimum sample size (considering a 10% non-response) will be 345 students. All the schools will have similar socio-demographic and built-environment characteristics [37]. School courses in Extremadura run from early September to mid-June, with a Christmas break from late December to early January and a break around March or April for the Easter holidays. As seen in Figure 1, assessments will be completed at baseline at the beginning of the school course (Term 1, February) and after the intervention (Term 2, June). A follow-up measurement will be conducted at the beginning of the following school course (Term 3, October). The study has been agreed upon by the Ethics Committee of the University of Extremadura (120/2018) and follows the guidelines of the Declaration of Helsinki.

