### 2.2. Intervention Based on SDT in Primary School

In February, an informative document will also be given to the families or legal guardians, accompanied by the informed consent to be signed. The research team will go to the schools to collect the data on certain days according to the organisational availability of the teachers during lessons. There will always be at least one research team member in the classroom while the students complete the questionnaires to solve any possible doubts. The questionnaires will be completed on paper in approximately 40 min. The variables described in Section 2.3 will be measured three times: (i) before the intervention (February); (ii) after the intervention (June); and (iii) a follow-up measure at the beginning of the following school year under the same conditions as in the two previous measures (October).

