Given that there is no set duration as the benchmark for an intervention programme to be effective, it was decided to set a duration that was in line with previous programmes carried out in primary education [36,40,41,42]. The intervention programme for promoting motivation and PA in primary schools will be carried out over approximately 4 months (March to June). During this period, the strategies that were co-created jointly with the PE teachers in the schools that form part of the experimental group will be developed. Approximately 10 strategies are expected to be developed to involve different agents (teachers, families, and peers) both in the school and in the out-of-school context. For instance, some possible strategies are introducing new physical-sports activities or sports modalities during free time, sharing the PA carried out outside the school context with the class, involving the families, organising complementary and extracurricular activities that encourage the practice of PA, etc. In this sense, each strategy will be associated with promoting a specific BPN, assuming that each one can favour at least one BPN. The reason for designing these strategies is to ensure that the students acquire a level of autonomy that determines when, how and why to do PA and adequate competence to manage the surrounding environment, face new challenges and acquire specific skills. Moreover, this sporting practice can be performed in the company of friends and family to generate a broader social bond, using PA as a nexus of union between people who intend to practice physical sports activities with other people for greater enjoyment. Each experimental school will carry out the same strategies. However, each teacher will be able to apply them as they see fit, adapting them to their own educational reality, under the supervision of a member of the research team (see Figure 2).

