*Engagement in Physical Education.* To assess students’ engagement in PE, we will use Skinner et al.’s [54] Student Engagement Questionnaire, adapted by Shen et al. [55]. The scale is preceded by the stem “When I am in PE class…”, and comprises 5 items (i.e., “I work as hard as I can”), which address students’ perceptions of their endeavour, heed, and steadfastness in PE classes. The response format is a Likert scale ranging from 1 (totally disagree) to 5 (totally agree).

*Academic Performance.* Reference to the grades obtained in the 2nd and 3rd trimesters in the subjects of PE, first language (Spanish), mathematics and second language (English). The grade point average (GPA) will then be calculated as an average of the scores in these four subjects. Previous studies have used these subjects as indicators to assess academic performance [56,57].

In addition, to evaluate the process and development of the school-based intervention, semi-structured interviews will be carried out with teachers, students and families in order to obtain complementary information to that obtained from the different questionnaires and scales mentioned above.

**Table 1 children-10-00504-t001:** Summary variables and instruments to measure them used in study.

Variable	Instrument
Socio-economic status	FAS Scale [46]
Height	Stadiometer
Weight	Weighing machine
Perceived Need Support in PA	PASSES [47]
Motivation toward physical activity	BREQ-3 [49]
Intention to be physically active	MIFA [51]
Perception of physical activity levels	PAQ-C [53]
Engagement in physical education	Physical Education Engagement Questionnaire [55]
Academic performance	Grades obtained in 1st and 2nd trimester

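### Academic performance is defined by 2nd and 3rd trimester grades in the text but by 1st and 2nd trimester grades in Table 1, and neither pair is likely to give a clean before-and-after comparison

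*Protocol article*

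**What the plan says.** The Academic Performance paragraph of Section 2.3 (protocol article) takes "Reference to the grades obtained in the 2nd and 3rd trimesters in the subjects of PE", together with Spanish, mathematics and English, and averages the four into a GPA. Table 1, which summarises the same section, lists the instrument as "Grades obtained in 1st and 2nd trimester". Section 2.4 names academic performance among the secondary outcomes and plans comparisons between groups and between pre-test and post-test.

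The timing information lies elsewhere:

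- **School year (Section 2.1):** "School courses in Extremadura run from early September to mid-June". The same section places one break at the turn of the year and another at Easter, which may fall in either March or April.
- **Intervention (Section 2.2):** it "will be carried out over approximately 4 months (March to June").
- **Assessment schedule (Section 2.2):** "The variables described in Section 2.3 will be measured three times", in February, June and October. The opening of Section 2.3 repeats these three months.
- **Wave labels (Section 2.1):** baseline is "at the beginning of the school course (Term 1, February"), the second wave is "after the intervention (Term 2, June"), and the October follow-up is called Term 3.

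The article gives no trimester dates and does not say which grade serves as baseline and which as outcome.

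**The concern.** One tested outcome has two incompatible definitions. Whoever analyses the data must choose between them, and if the choice is made with grades in hand it is a free analytic decision.

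The choice also changes what is measured. A pre/post contrast needs one grade earned wholly before the intervention and one that reflects it as fully as possible. Set against the school calendar, the Table 1 pair appears to lack the second and the text pair appears to lack the first. In addition, two grade points cannot fill a three-wave schedule, so the article does not show how grades enter the repeated-measures analysis.

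**Working it through.** There is no stated figure to reproduce. The check is a comparison of the definitions followed by date arithmetic.

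**1. The definitions side by side**

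| Source | Grades used | Time points |
|---|---|---|
| Section 2.3, text | 2nd and 3rd trimester | 2 |
| Section 2.3, Table 1 | 1st and 2nd trimester | 2 |
| Section 2.2 and opening of Section 2.3 | all Section 2.3 variables | 3 |

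The two pairs share only the 2nd trimester.

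**2. Assumptions for the calendar check.** The article gives months, not dates, so these are mine. The intervention runs from 1 March to 15 June, which is 106 days. The 2nd trimester runs from 8 January to the start of the Easter break, taken as 13 March (early), 31 March (middle) or 16 April (late), because Section 2.1 allows March or April.

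**3. Overlap of the 2nd trimester with the intervention.** Overlap = trimester end minus 1 March.

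| Easter break starts | Length of trimester 2 (days) | Overlap (days) | Share of trimester 2 | Share of intervention | Days from trimester end to 15 June |
|---|---|---|---|---|---|
| 13 March | 64 | 12 | 12/64 = 19% | 12/106 = 11% | 106 − 12 = 94 |
| 31 March | 82 | 30 | 30/82 = 37% | 30/106 = 28% | 106 − 30 = 76 |
| 16 April | 98 | 46 | 46/98 = 47% | 46/106 = 43% | 106 − 46 = 60 |

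In weeks, the overlap is 12/7 ≈ 2 to 46/7 ≈ 6.5.

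**4. Alternative trimester rule.** Splitting 10 September to 15 June into equal thirds puts the end of the 2nd trimester at about 14 March. The overlap is then 13 days, or 14% of the trimester.

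**5. Alternative start dates (overlap in days)**

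| Intervention starts | Early Easter | Middle | Late |
|---|---|---|---|
| 8 March | 5 | 23 | 39 |
| 15 March | 0 | 16 | 32 |
| 31 March | 0 | 0 | 16 |

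The overlap disappears only when the programme starts once the Easter break has begun. That sits poorly with a programme of about four months from March: a start on 1 March already gives only 106 days, and a start on 15 March leaves 106 − 14 = 92.

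**6. What each pair can show under these assumptions**

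- *Table 1 pair.* The 1st trimester is wholly before March. The 2nd closes 60 to 94 days before the programme ends. The pair can register an effect that arises in the first weeks, but nothing later.
- *Text pair.* The 3rd trimester lies within the intervention and ends with it, so it is the natural outcome grade. The 2nd is the only available baseline and includes exposed weeks. If E is the effect on the 3rd-trimester grade and a fraction f of it is already present in the 2nd-trimester grade, the pre/post contrast estimates E(1 − f). The article gives nothing from which to estimate f. If no effect appears early, f is 0 and nothing is lost.

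**7. Other meaning of the word.** If trimester means the Term 1, 2 and 3 labels of Section 2.1 (February, June, October), the Table 1 pair becomes before and after, and the text pair becomes after and follow-up, with no baseline. The consequences change, but the two definitions still disagree.

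**The case against.** The strongest reply accepts the mismatch and disputes what follows from it. The article gives no trimester dates and never calls any grade a baseline or an outcome, so the overlap is inference. With an early Easter it is only about 12 days, and with a later start it could be nil. The Term labels in Section 2.1 offer a reading under which Table 1 is a sound pre/post pair. The three-wave sentence sits in a paragraph about classroom questionnaires, and grades are records with timing of their own. All of this stands as a limit on the consequences, which are therefore given as conditional and as ranges. None of it removes the contradiction.

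A reader might infer two stronger things, and the documents support neither.

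- *That the Table 1 version makes the outcome unable to show any effect.* On the calendar above, 11% to 43% of the intervention falls before the 2nd trimester closes. Exposure is reduced and late effects are missed, but an early effect could still appear.
- *That the PE mark should leave the GPA because the teacher delivering the programme also awards it.* The article does not say who awards the PE mark. The four-subject average is a deliberate choice supported by cited precedent, and resolving the trimester conflict does not require redefining it.

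**Conclusion.** The contradiction is certain: the text and Table 1 of Section 2.3 define the same secondary outcome by different trimesters, and no other section resolves it. The mismatch with the three-wave schedule is also literal, though minor.

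The consequences are probable rather than certain. They rest on trimesters ending at the school breaks (or at equal thirds of the year) and on a start at the beginning of March. On that footing, the Table 1 pair has no grade from the last 60 to 94 days of the programme, and the text pair has a baseline that includes about 2 to 6.5 weeks of it, which could dilute a pre/post contrast by an unknown amount. The primary outcome, motivation for out-of-school physical activity, is not affected. The point should be corrected before grades are analysed.

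**What to change.** Make the Academic Performance paragraph and Table 1 agree. Use 1st-trimester grades, which fall wholly before March under either trimester rule, as the pre-intervention value and 3rd-trimester grades as the post-intervention value. Give the closing date of each grading period, so that the meaning of trimester no longer depends on the Term labels in Section 2.1. Report 2nd-trimester grades descriptively. Keep the four-subject GPA as defined. Add a sentence saying that grades are taken from these periods and are not part of the February, June and October schedule.

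The cost is one correction to the text and table, and one further grade extraction beyond those the text already calls for, assuming that schools hold the 1st-trimester grades. The planned pre/post comparison can be used with this pair as it stands.

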### 1.3. The Present Study

In accordance with the previous studies and the theoretical framework of SDT, we highlighted that: (a) most of the studies were based on different theories; (b) they assessed only variables within PE; (c) they were applied to young people over 12 years of age; (d) PE teachers were not always involved in the intervention; and (e) most of the strategies developed only focused on autonomy support. Therefore, this study aims for the PE teacher to apply a series of SDT-based motivational strategies that support autonomy, competence, and relatedness towards PA in primary education students to improve their motivation for PA and, consequently, their extracurricular PA. For this purpose, an intervention will be carried out in students (10 to 12 years), where strategies will be applied to support the three BPNs (i.e., autonomy, competence, and relatedness) concerning PA and with the teachers playing a more active role, as they will co-create and develop these motivational strategies to promote motivation and out-of-the-school practice of PA.

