#### 2.1.2. Teachers’ Training Program

PE teachers from participating schools will be involved in a training programme on motivational strategies. The research team will contact teachers who decide to participate in the project by e-mail or mobile phone. This contact aims to guarantee their participation in the project and present the objectives and characteristics of the intervention programme. Teachers who join the PE staff after the intervention programme should establish contact to ensure the full development of the programme. The research team will provide each teacher with a document about the objectives to be achieved in the project and the methodology to be implemented.

Regarding the training programme, at least two sessions will be held in February with the teachers whose schools were designated as the experimental school, each lasting 4 h. In the first session, the explanation and timing of the project and its theoretical basis will be presented. Firstly, the research team will explain the fundamentals of SDT applied to PE, underscoring the promotion of PA practice based on supporting the BPNs. Secondly, the teachers will be divided into work groups for a brainstorming session to co-create different intervention strategies where this theoretical basis can be put into practice to promote autonomy, competence, and relatedness towards PA. These strategies will be shared with the rest of the teachers and supervised by the research team. During the second training session, the research team and the teachers will discuss these strategies’ feasibility and functionality to promote PA both in educational and extracurricular contexts. In other words, the ideas developed in the brainstorming session can be adapted correctly and appropriately to the schools’ educational reality. In addition, the research team will arrange weekly meetings with the teachers to obtain feedback on the strategies developed.

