### 2.4. Statistical Analysis

The primary outcome will be changes in the levels of students’ motivation for out-of-school PA. Secondarily, perceived exercise autonomy support, the intention to be physically active, perception of PA levels, engagement in PE and academic performance will also be assessed. For this purpose, firstly, the nature of the variables will be taken into account through the application of normality, validity, and reliability tests. Secondly, the principles of independence, normality, linearity and variance of the study variables will be tested for general linear model analyses. Thirdly, intergroup and intragroup differences will be analysed with repeated-measures ANOVA or nonparametric tests such as McNemar’s or the Kruskall–Wallis tests, as appropriate. For continuous variables, Bonferroni-corrected multiple paired *t*-tests will be calculated to determine intra-group (i.e., between the experimental and control group) and inter-group (i.e., between the pre-test and post-test) differences. For categorical variables, a chi-square test will be performed. While Cramer’s V will be used to describe the degree of association between categorical variables and experimental and control schools, McNemar’s test will be used to analyse baseline and post-intervention differences in categorical variables in experimental and control schools, respectively. Effect sizes will be assessed using Partial Eta Squared (η_p_^2^) and Cramer’s V values for continuous and categorical variables, respectively. Effect sizes will be considered small, moderate or large when η_p_^2^ is greater than 0.01, 0.06 and 0.14, respectively, and when Cramer’s V is greater than 0.10, 0.30 and 0.50, respectively. Significance will be set at *p* < 0.05 for all analyses.

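### The academic performance GPA gives one quarter of its weight to PE, a grade presumably awarded by the teacher who delivers the programme, so an arm difference may partly reflect PE alone

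*Protocol article*

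**What the plan says.** Section 2.3 of the protocol article takes academic performance from "grades obtained in the 2nd and 3rd trimesters in the subjects of PE, first language (Spanish), mathematics and second language (English"). It then combines them: "The grade point average (GPA) will then be calculated as an average of the scores in these four subjects". No weights are given, so a plain average is the natural reading. Section 2.4 lists the result among the secondary outcomes: "engagement in PE and academic performance will also be assessed".

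Table 1, which closes the same section, names a different pair of grading periods, the first and second trimester.

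On the PE teacher's part in the programme:
- Training (2.1.2): "at least two sessions will be held in February with the teachers whose schools were designated as the experimental school".
- Design and delivery (2.2), in a programme running from March to June: "the strategies that were co-created jointly with the PE teachers in the schools that form part of the experimental group will be developed".
- Discretion (2.2): "each teacher will be able to apply them as they see fit, adapting them to their own educational reality".

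The article does not say who awards the PE grade. It describes no external or standardised grading and no GPA without PE.

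**The concern.** The PE teachers in the experimental schools cannot be unaware of their arm, because they help to design the programme and then run it. If they also mark PE, the person delivering the intervention scores one quarter of this outcome. A change in how effort or participation is marked would then enter the GPA as if pupils' academic work had improved. The article describes no matching involvement of control-school teachers.

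There is a second route that needs no grading bias. The programme is delivered through PE, so a genuine gain could be confined to PE. Averaged with three other subjects and labelled academic performance, it would read as a general academic benefit.

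What is at stake is the interpretation of one secondary outcome. Motivation for out-of-school physical activity, the primary outcome, does not use grades.

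**Working it through.** The article states no figure for this outcome, so there is none to reproduce. The check has two parts.

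**1. How much a PE-only shift moves the GPA**

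Inputs from the article: four subjects averaged (2.3), and a small effect defined as partial eta squared greater than 0.01 (2.4).

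Assumptions, none of them stated: equal weights, a 0 to 10 grade scale, a GPA SD of 1.2 to 1.5, and a mean PE shift b of 0.5 to 1.0 point in experimental schools with no change in the other subjects.

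Formulas: GPA shift = b/4; d = (b/4)/SD; for two equal groups, eta squared = d²/(d² + 4).

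| PE shift b | GPA shift | SD | d | eta squared |
|---|---|---|---|---|
| 0.5 | 0.125 | 1.5 | 0.083 | 0.0017 |
| 0.5 | 0.125 | 1.2 | 0.104 | 0.0027 |
| 1.0 | 0.25 | 1.5 | 0.167 | 0.0069 |
| 1.0 | 0.25 | 1.2 | 0.208 | 0.0107 |

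Only the last row exceeds 0.01. Setting eta squared to 0.01 gives d² = 0.04/0.99, so d = 0.201. The PE shift needed is 4 × 0.201 × SD: about 0.96 points at SD 1.2 and about 1.21 points at SD 1.5. The second lies outside the assumed range.

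Section 2.4 plans a repeated-measures ANOVA, where the SD of change matters: SD of change = SD × √(2(1 − r)), with r the correlation between the two GPAs. At r = 0.5 the factor is 1 and the table stands. At r = 0.8 (also an assumption) the factor is 0.63. A 1.0-point shift then gives about 0.017 to 0.026, and a 0.5-point shift about 0.004 to 0.007.

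As an illustration of false positives, take the article's minimum of 345 pupils split equally (172.5 per arm), two-sided 0.05, SD 1.5, and clustering by school ignored. The standard error is 1.5 × √(2/172.5) = 0.162. With no true effect, the chance of p < 0.05 is about 12% for a 0.5-point PE shift and 34% for a 1.0-point shift, against a nominal 5%.

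**2. Whether the route is open at all**

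Under the text of 2.3, third-trimester grades count and the programme runs from March to June, so these grades are given during or after delivery and the route is open. Under Table 1, most grading would probably precede the programme. The bias would then be small, but the outcome could hardly detect an effect either.

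The article does not date the trimesters. Section 2.1 attaches its own labels to the assessments (Term 1 for February, Term 2 for June), so Table 1 might be following those. That cannot be settled from the document.

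**The case against.** The strongest objection is that the mechanism rests on inference. The article does not say that the PE teacher awards the PE grade, and nothing in it shows that teachers would mark more generously. The weekly monitoring in 2.1.2 and 2.2 concerns feedback on the strategies and how far they are carried out, not pupils' marks. This stands as a limit: the grader's identity is the natural reading but only a presumption, and the size of any shift is unknown.

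A reader might infer that PE grading alone would lift the GPA to a small effect on the article's own scale. The documents do not support that. Scale, SD and shift are all assumed, and in the simple comparison only the largest shift with the smallest SD exceeds 0.01. Even a d of 0.2 gives 0.04/4.04 = 0.0099, just short.

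A reader might also infer that the PE grade should never be cited as evidence of benefit. That goes too far. Section 1.1 reports that need-supportive teaching predicts performance in PE, so PE is where a real effect is expected, and grades alone cannot separate that from lenient marking. This argues for showing PE separately, not for discarding it.

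Finally, the four-subject GPA has cited precedent, and a breakdown by subject could appear in a fuller plan. The article presents that precedent as support for these subjects as indicators. It does not address grading by the person who delivers the intervention. The composite itself is fixed in the article, so its definition is open to comment here.

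**Conclusion.** The point holds in a limited form. As 2.3 is written, PE is one quarter of academic performance, and the experimental-school PE teachers know their arm and deliver the programme. If they award the PE grade and third-trimester grades are used, an arm difference in GPA can partly reflect PE grading or a PE-only effect.

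Under the assumed ranges the contribution is about 0.08 to 0.21 SD of GPA. In a simple two-group comparison it passes the article's threshold for a small effect only at the extreme. It could be larger in a repeated-measures analysis with highly correlated grades. The documents do not show that such a shift will occur. The trimester conflict between the text of 2.3 and Table 1 must be resolved, because it decides whether the route exists.

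**What to change.** In 2.3 and Table 1:

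1. Define academic performance as the mean of the Spanish, mathematics and English grades.
2. Report the PE grade separately, with a note that it may be awarded by the unblinded programme teacher. State who awards it, if known.
3. Keep the four-subject GPA as a supplementary result, for comparability with earlier studies.
4. State one pair of trimesters in both places and say how they fall relative to the March to June programme.

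This removes the direct contribution of PE grading to the main academic figure, from b/4 to zero. It needs a few sentences and no new data, since grades are already obtained by subject. The price is a composite that is slightly noisier with three components and less comparable with earlier four-subject GPAs; item 3 limits the second loss.
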